### Provisions for post-trial care {30}

All participants are covered by the sponsor’s insurance policy, which is in accordance with the Dutch law (Medical Research Involving Human Subjects Act (WMO), article 7). This insurance provides cover for damage to research participants through injury or death caused by the study. The insurance applies to damage that becomes apparent during the study or within 4 years after the end of the study. Any complications caused by study-related procedures will be treated according to the current protocols of treatment, based on current literature.

### Outcomes {12}

#### Primary outcome

The primary outcome is the difference in wrist function, measured with the Patient-Rated Wrist Evaluation (PRWE) at 3 months compared to baseline. The PRWE is a measure of pain and wrist function in activities of daily living. The PRWE will be measured as a secondary outcome at 6 and 12 months.

#### Secondary outcomes

The following secondary outcome measures will be measured at baseline, 3 months, 6 months and 12 months (Table 1):Range of motion (ROM) of the wrist measured using a standard goniometer, including pronation, supination, ulnar and radial deviation, and palmar and dorsal flexionGrip strength of the wrist measured using a dynamometer (Saehan). Grip strength will be calculated as the mean of three attemptsNumeric Rating Scale (NRS) pain scale. A score of 0 indicates no pain, and a score of 10 indicates the worst possible painEULAR response rate and Disease Activity Score (DAS28)Resolution of synovitis measured by wrist ultrasound in grey scale and power Doppler mode (baseline and 3 months only)Wrist arthritis and joint destruction on standard (plain) radiographs of the wrist (baseline and 12 months only)Quality of life measured with the EuroQol 5D (EQ-5D-5L) questionnaireBlood parameters including erythrocyte sedimentation rate (ESR) and C-reactive protein (CRP) (part of the routine clinical care)Complications and subsequent treatment

**Table 1 Tab1:** Trial schedule according to the recommendation for interventional trial (SPIRIT) guidelines

	Enrolment	Allocation	Post-allocation					
Timepoint**	*14 days (*± *4 days) prior to intervention*	Intervention	*Week 2*	*Week 4*	*Week 6*	*Month 3*	*Month 6*	*Month 12*
Enrolment								
Eligibility screen	X							
Informed consent	X							
Allocation	X							
Interventions								
Arthroscopic synovectomy		X						
Intra-articular corticosteroid injection		X						
Assessments								
Questionnaires (PRWE, EQ-5D-5L, iMCQ, iPCQ)	X					X	X	X
Physical exam (including ROM, GS and DAS28)	X					X	X	X
Wrist ultrasound	X					X		
Plain wrist radiographs	X							X
Blood parameters (ESR, CRP)	X					X	X	X
NRS pain scores	X		X	X	X	X	X	X
Complications and secondary treatment			X	X	X	X	X	X
Cost-effectiveness analysis								X

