#### Intra-articular corticosteroid injections (IACSI)

Forty milligrammes of triamcinolonacetonide (1 ml of 40 mg/ml Kenacort-A) will be injected into the joint under palpation guidance using a 21G (green) needle or 23G (blue) needle. A pressure dressing will be applied for 8 h. Patients can start exercising the wrist immediately. The procedure will take approximately 5 min.

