### Strategies to improve adherence to interventions {11c}

All study visits are planned simultaneously with the routine visits with the rheumatologist to minimize patient burden and improve study adherence. Patients will be contacted by telephone 2, 4 and 6 weeks after the intervention to obtain pain scores and to answer questions from the patient. All study questionnaires can be completed digitally within a 14-day timeframe. A reminder will be sent after 10 days.

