## Data collection and management

### Plans for assessment and collection of outcomes {18a}

Baseline data will be derived from the electronic patient record. Standard protocol for rheumatic patients in the Maasstad Hospital requires a 3-month follow-up with DAS28 scores, blood parameters and physical examination. In case of persistent wrist inflammation, regular wrist ultrasounds and yearly wrist radiographs are indicated. All laboratory tests, ultrasounds and radiographs will be performed in the Maasstad Hospital according to regular standards. NRS pain scores at 2, 4 and 6 weeks after the intervention will be obtained by phone call. Questionnaires will be sent to patients digitally using the Castor survey application [30]. All data will be collected with an electronic case report form (eCRF) in Castor EDC.

The primary outcome will be measured using the PRWE, which is a self-reported questionnaire that consists of 15 questions regarding pain and disability of the wrist when performing daily activities [31]. The highest score is 100 and indicates severe disability, and the lowest score is 0 and indicates no disability. The PRWE has been validated for patients with rheumatoid arthritis and for the Dutch language [27, 32]. Also, normative data and the minimal clinically important difference have been calculated for the PRWE [28, 29].

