Secondary outcomes include the EULAR response rate, reduction of synovitis on wrist ultrasound, progression of wrist arthritis on plain radiography and quality of life. DAS28 scores are used to determine the EULAR response rate, which measures responsiveness to anti-rheumatic treatment. The DAS28 is a composite measure of disease activity in rheumatic patients calculated by evaluating 28 joints for swelling and tenderness, combined with NRS pain scores and C-reactive protein levels in the blood. Wrist ultrasound, performed by one of two experienced rheumatologists, is used to measure the resolution of synovitis and is scored using the EULAR-OMERACT combined scoring system which combines grey scale and power Doppler mode [33]. Ultrasound has demonstrated greater sensitivity than clinical assessment and conventional radiography for detecting synovitis in RA target joints [34, 35]. Standard wrist radiographs will be graded using the modified Larsen grading system, which scores degenerative wrist arthritis and joint destruction on a score of 0 to 5, 5 indicating the most joint abnormalities [36, 37]. The EuroQol 5D (EQ-5D-5L) questionnaire is a widely used standardized questionnaire scoring overall quality of life using five different 5-level domains, on a scale from 0 to 100. It has been validated and translated to Dutch [38, 39]. A cost-effectiveness analysis will be performed based on medical costs and productivity loss (see the ‘Methods for additional analyses (e.g. subgroup analyses) {20b}’ section). The iMTA Productivity Cost Questionnaire is a standardized instrument for measuring and valuing health-related productivity losses and estimated societal costs based on educational level, job type and lost workdays [40]. The iMTA Medical Consumption Questionnaire (iMCQ) is a standardized instrument including questions related to frequently occurring contacts with health care providers, medication use and home care [40]. Medical resource prizes will be obtained from the Dutch Healthcare Authority [41]. From these costs, cost-effectiveness will be calculated in relation to quality-adjusted life years (QALYs) using the EQ-5D-5L (or PRWE) over a 1-year and 5-year span.

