#### Cost-effectiveness analysis

Costs include direct medical costs (professional time, laboratory tests, diagnostic procedures, drug therapies, medical admissions and surgical admissions), direct non-medical costs (help at home and selfcare, help devices, transportation and home remodelling) and indirect costs (lost productivity in employed patients, lost productivity in family members caring for the patient). The direct costs of each patient will be obtained from the financial data of the Maasstad Hospital. The indirect costs of each patient will be measured on the basis of the filled-out iMTA Medical Consumption Questionnaire (iMCQ) and iMTA Productivity Cost Questionnaire (iPCQ) questionnaire. These measured costs will be valued with the friction cost method.

After all the costs and utilities are obtained, the incremental cost-effectiveness ratio (ICER) will be calculated with the following formula:$$\mathrm{ICER}=\frac{\mathrm{Cost}\;\mathrm{of}\;\mathrm{arthroscopic}\;\mathrm{synovectomy}-\mathrm{Cost}\;\mathrm{of}\;\mathrm{IACSI}}{\mathrm{Effect}\;\mathrm{of}\;\mathrm{arthroscopic}\;\mathrm{synovectomy}-\mathrm{Effect}\;\mathrm{of}\;\mathrm{IACSI}}$$

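### No EQ-5D-5L is taken between enrolment and month 3, so QALYs cannot show an early loss after surgery and may favour arthroscopy by an unknown amount

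*Protocol article*

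**What the plan says.** Under Secondary outcomes the article states: "The following secondary outcome measures will be measured at baseline, 3 months, 6 months and 12 months". The EQ-5D-5L is on that list. Table 1 gives the same visits for the whole questionnaire row, "Questionnaires (PRWE, EQ-5D-5L, iMCQ, iPCQ", with enrolment set at 14 days (± 4 days) before the intervention. Weeks 2, 4 and 6 are marked for NRS pain and for complications and secondary treatment, and not for any questionnaire. Section {11c} describes those early contacts: "Patients will be contacted by telephone 2, 4 and 6 weeks after the intervention to obtain pain scores". Section {18a} repeats this: "NRS pain scores at 2, 4 and 6 weeks after the intervention will be obtained by phone call".

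On the use of the data, section {18a} says that "cost-effectiveness will be calculated in relation to quality-adjusted life years (QALYs) using the EQ-5D-5L", with the PRWE as an alternative and horizons of one and five years: "using the EQ-5D-5L (or PRWE) over a 1-year and 5-year span". The Cost-effectiveness analysis section gives an ICER formula. It takes direct costs from hospital records ("The direct costs of each patient will be obtained from the financial data of the Maasstad Hospital") and indirect costs from the iMCQ and iPCQ, valued by the friction cost method.

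The two treatments differ in their immediate burden. Arthroscopy is day surgery of about 60 minutes under general anaesthesia or plexus block, with four portals, a 48-hour dressing and a wound check at 10 to 14 days. For the injection the article says: "Patients can start exercising the wrist immediately. The procedure will take approximately 5 min". Both arms receive 40 mg of triamcinolonacetonide in the wrist.

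**The concern.** A QALY is the area under a utility curve, and the curve is known only where utility is measured. Here the first point after treatment is at month 3. Any temporary loss in the first weeks leaves no trace if the patient has recovered by then. The PRWE does not fill the gap, because it sits in the same row of Table 1.

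The gap would matter little if it affected both arms alike. The steroid is common to both, so its early effect is broadly shared. Surgery, anaesthesia and wound healing are not. An extra early loss in the arthroscopy arm would go unseen and would not cancel in the difference. The QALY difference in the ICER denominator would then be too favourable to arthroscopy.

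This is a question of what is collected, so an analysis plan that is not shown could not repair it: no analysis can recover utilities that were never recorded. At stake is the cost-effectiveness comparison, a named objective of the trial, though a secondary one.

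**Working it through.** The plan states no figure on this point. The sample size rests on the PRWE at 3 months and uses none of the data at issue, so it is not affected.

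**Inputs from the article.** EQ-5D-5L at enrolment and months 3, 6 and 12; month 3 is about 13 weeks after the procedure; horizons of 1 and 5 years.

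**Assumptions, not in the article.** The extra utility dip after arthroscopy over that after injection is *d*, lasting *w* weeks. Each EQ-5D-5L describes the patient's state at that visit. Enrolment and month 3 are joined by a straight line, and *d* is measured from that line. The range taken is *d* = 0.1 to 0.3 and *w* = 2 to 6.

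**Missed QALY per arthroscopy patient.** If the dip stays constant and then ends (rectangular), the loss is *d* × *w*/52. If it recovers linearly, the loss is half of that.

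| *d* | *w* (weeks) | Rectangular | Linear |
|---|---|---|---|
| 0.1 | 2 | 0.1 × 2/52 = 0.0038 | 0.0019 |
| 0.2 | 4 | 0.2 × 4/52 = 0.0154 | 0.0077 |
| 0.3 | 6 | 0.3 × 6/52 = 0.0346 | 0.0173 |

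The range is therefore about 0.002 to 0.035 QALY.

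**Set against an illustrative benefit.** Suppose arthroscopy gives a utility gain of 0.05, reached linearly by month 3 and then held.

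- Over 1 year the gain is 0.05 × (0.25/2 + 0.75) = 0.0438 QALY. The missed loss is 0.0038/0.0438 = 9% to 0.0346/0.0438 = 79% of it if rectangular, and about 4% to 40% if linear.
- Over 5 years, undiscounted, the gain is 0.05 × (0.125 + 4.75) = 0.244 QALY. The missed loss is about 2% to 14% of it if rectangular, and about 1% to 7% if linear. This requires the gain to persist well beyond the 12 months of follow-up.

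Read the other way, a missed loss of 0.0154 QALY cancels the 1-year gain from a sustained utility benefit of 0.0154/0.875 = 0.018.

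**Productivity.** If the iPCQ at month 3 looks back *r* weeks, the uncovered time after treatment is 13 − *r* weeks: none for a 13-week recall, 9 weeks for a 4-week recall. The article gives no *r*, so whether there is a gap at all cannot be settled from it.

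**Direct costs.** These come from hospital financial data and do not depend on questionnaire dates.

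**The case against.** The strongest reply is that nothing in the article shows a material early loss. Patients are told to mobilise the wrist at once after arthroscopy, the dressing stays on for two days, and the background describes little postoperative pain and quick recovery. A constant loss of 0.3 for six weeks is then a worst case. This stands as far as size goes. It does not remove the point: the favourable description of recovery is relative to open synovectomy, not to an injection, and an instruction to mobilise is not a measurement.

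Second, the article gives no interpolation rule, and a condensed article may leave one, or a procedural decrement, to the full plan. That also stands, so the straight line is an assumption here. But any rule that uses only enrolment and month 3 has no information about the weeks between.

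Third, the early weeks are not empty. Table 1 records pain, complications and secondary treatment at weeks 2, 4 and 6. These can inform assumptions about early loss, but they are neither utilities nor counts of lost workdays.

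A reader might infer that both the QALY and the cost results are certainly biased towards arthroscopy. The documents do not support that. Direct costs are outside the problem. The iPCQ counts lost workdays, which is a look-back measure, so a month-3 questionnaire could cover the whole interval. Even the direction is likely rather than certain: the article cites accurate placement in only 66% of palpation-guided injections, so an early steroid benefit could be greater after arthroscopy, and that too would go unmeasured.

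**Conclusion.** The point holds in a limited form. The schedule leaves about 13 weeks after treatment without a utility measurement, in a comparison of day surgery with a five-minute injection. If surgery causes the larger early loss, QALYs from these visits will favour arthroscopy. Under the stated assumptions the amount is about 0.002 to 0.035 QALY per arthroscopy patient. That ranges from negligible to a large share of a modest 1-year gain, and it is a much smaller share over five years if the gain lasts. The documents cannot place the true value within or outside this range.

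Productivity costs are at risk only if the iPCQ recall is shorter than about 13 weeks. The primary PRWE comparison, the sample size and the direct costs are untouched. This is an inexpensive improvement to a secondary analysis, not a flaw in the main result.

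**What to change.** For patients still to be treated, add the EQ-5D-5L at the existing week 2, 4 and 6 contacts in both arms, through the Castor survey already in use, and use these points in the QALY calculation. State the iPCQ recall period. If it does not span the interval to month 3, add short absence items at the same contacts. State how utility is joined between visits.

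For patients already past week 6, do not impute early values from later patients as the main analysis, since that rests on an assumption that cannot be tested. Pre-specify a sensitivity analysis over a range of early decrements, such as the range above, with the recorded NRS pain scores as a guide. Apply it also to the days before week 2, because a first questionnaire at week 2 could largely miss a dip lasting only two weeks. Report the ICER with and without the early data.

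The cost is a few minutes per patient, a Castor change and an amendment. The limit is coverage: recruitment began in January 2021 and was expected to finish in 2023, so early data would exist for only part of the sample. The sensitivity analysis needs no new data and can be done in any case.

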#### Other study parameters

At baseline, the following data will also be collected: gender, age, smoking status, duration of disease, previous anti-rheumatic treatment, analgesics and a medical history of cardiopulmonary disease, diabetes, malignancy, auto-immune disease, wrist trauma and osteoporosis.

### Participant timeline {13}

The schedule of enrolment, interventions and assessments is outlined in Table 1.

### Sample size {14}

The sample size was calculated for the primary endpoint, the difference in PRWE scores at 3 months. According to one study, the median PRWE score in RA patients is 20.0 (IQR: 9.8–48.3) for the dominant hand and 22.8 (IQR 6.9–38.6) for the non-dominant hand, but means and standard deviations for RA are not known [27]. The mean PRWE score among the general population was estimated as 7.7 with a standard deviation of 15.0 [28]. The minimal clinically important difference of the PRWE is 11.0 points [29]. We hypothesize that a mean difference of at least 11.0 points on the PRWE score could be encountered between the two groups after 3 months. A simulation study using *K* = 1000 random draws per sample size from a multivariate normal distribution was performed to estimate the power for several sample sizes, where the significance of the treatment effect was estimated by a linear mixed model (likelihood ratio test). Assuming a (conservative) correlation of 0.1 between PRWE at baseline and at 3 months and a standard deviation of 15.0, it was found that at *α* = 0.05 and power of 90%, 38 patients per treatment arm would be required. To correct for the expected loss to follow-up of 5%, 40 patients in each arm will be included.

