**Methods:**

This protocol describes a prospective, randomized controlled trial. RA and PsA patients are eligible with prominent wrist synovitis objectified by a rheumatologist, not responding to at least 3 months of conventional DMARDs and naïve to biological DMARDs. For 90% power, an expected loss to follow-up of 5%, an expected difference in mean Patient-Rated Wrist Evaluation score (PRWE, range 0–100) of 11 and *α* = 0.05, a total sample size of 80 patients will be sufficient to detect an effect size. Patients are randomized in a 1:1 ratio for arthroscopic synovectomy with deposition of corticosteroids or for IACSI. Removed synovial tissue will be stored for an ancillary study on disease profiling. The primary outcome is wrist function, measured with the PRWE score after 3 months. Secondary outcomes include wrist mobility and grip strength, pain scores, DAS28, EQ-5D-5L, disease progression on ultrasound and radiographs, complications and secondary treatment. Additionally, a cost-effectiveness analysis will be performed, based on healthcare costs (iMCQ questionnaire) and productivity loss (iPCQ questionnaire). Follow-up will be scheduled at 3, 6 and 12 months. Patient burden is minimized by combining study visits with regular follow-ups.

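### The 90% power rests on a general-population SD of 15.0, while the RA quartiles quoted beside it imply an SD of roughly 21 to 28.5 and clearly lower power

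*Protocol article*

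**What the plan says.** The Sample size section (item 14) of the protocol article sets out its inputs in one paragraph. For RA it reports that the "median PRWE score in RA patients is 20.0 (IQR: 9.8–48.3) for the dominant hand and 22.8 (IQR 6.9–38.6) for the non-dominant hand", and adds that RA means and SDs are not known. It then turns to a different population: "The mean PRWE score among the general population was estimated as 7.7 with a standard deviation of 15.0". The target effect is the minimal clinically important difference: "We hypothesize that a mean difference of at least 11.0 points on the PRWE score could be encountered between the two groups after 3 months".

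The simulation draws from a multivariate normal distribution and tests the treatment effect by a likelihood ratio test in a linear mixed model, "Assuming a (conservative) correlation of 0.1 between PRWE at baseline and at 3 months and a standard deviation of 15.0". The result: "it was found that at *α* = 0.05 and power of 90%, 38 patients per treatment arm would be required". Allowing for 5% loss to follow-up gives 40 per arm. The Methods part of the abstract repeats the 90% power and says that 80 patients in total will be sufficient.

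The article gives no reason why the general-population SD should apply to the trial's patients, and reports no result for a larger SD. Only the correlation is described as conservative.

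**The concern.** Saying that RA standard deviations are unknown does not leave the RA spread unknown, because the quartiles describe it. The SD actually used comes from people with a mean of 7.7 on a 0–100 scale, most of them close to the floor, where scores have little room to vary. RA patients in the same paragraph have medians of 20.0 and 22.8 and upper quartiles of 48.3 and 38.6.

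Sample size grows with the square of the SD, so this input matters more than the correlation, the one input set cautiously. At stake is the only justification given for 80 patients on the primary endpoint. The Interim analyses section plans none, and the article describes no sample-size re-estimation, so nothing in it would bring an understated SD to light before the final analysis.

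**Working it through.** **Inputs** (Sample size section unless noted): difference 11.0; SD 15.0; correlation ρ = 0.1; α = 0.05, taken as two-sided because sidedness is not stated; n = 38 per arm; 5% loss. The model (Statistical methods section) puts baseline in the outcome vector with time and treatment × time and lists no treatment main effect. The arms therefore share a baseline mean, and the model is as efficient as analysis of covariance.

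**Formulas.** SE = √[2·SD²·(1 − ρ²)/n]. Power ≈ Φ(11/SE − 1.96). Difference detectable with 90% power = (1.960 + 1.282)·SE.

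**Step 1: reproduce the plan.** SE = √[2·225·0.99/38] = 3.42. 11/3.42 = 3.21. Power = Φ(1.25) = 89.5%. The formula needs 38.7, so 39 per arm; a likelihood-ratio simulation with 20,000 draws gives 89.2% at 38. Inflation: 38/0.95 = 40. The stated 38 and 40 follow from the stated inputs.

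**Step 2: the spread in the RA quartiles.**
- A normal variable with SD 15 has an interquartile width of 1.349 × 15 = 20.2.
- Dominant hand: 48.3 − 9.8 = 38.5; 38.5/1.349 = 28.5.
- Non-dominant hand: 38.6 − 6.9 = 31.7; 31.7/1.349 = 23.5.
- The dominant-hand quartiles are skewed: 20.0 − 9.8 = 10.2 below the median, 48.3 − 20.0 = 28.3 above it. A beta distribution on 0–100 fitted to each set of quartiles gives SDs of 25.9 (dominant) and 21.1 (non-dominant).

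**Step 3: power at 38 per arm for a difference of 11.**

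| SD | Basis | Power, ρ = 0.1 | Power, ρ = 0.5 | Detectable with 90% power, ρ = 0.1 |
|---|---|---|---|---|
| 15 | plan | 89.5% | 96% | 11.1 |
| 20 | assumed narrowing by selection | 67% | 79% | 14.8 |
| 21 | beta fit, non-dominant | 63% | 75% | 15.5 |
| 23.5 | normal, non-dominant | 54% | 65% | 17.4 |
| 26 | beta fit, dominant | 46% | 57% | 19.2 |
| 28.5 | normal, dominant | 39% | 49% | 21.1 |

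Likelihood-ratio simulation at ρ = 0.1 agrees: 53.7% at SD 23.5 and 40.0% at SD 28.5.

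**Step 4: can a higher correlation make up the gap?** Matching the plan's residual SD of 15·√0.99 = 14.92 requires ρ = √[1 − (14.92/SD)²], which is 0.77 for SD 23.5 and 0.85 for SD 28.5.

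**The case against.** Several counter-arguments have weight.

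- **Nothing is miscalculated.** True. The fault is in the choice of SD, and a reader who infers an arithmetic error would be mistaken.
- **A power of 39–54% is the pessimistic end.** A reader might take that range, from SDs of 28.5 and 23.5 at ρ = 0.1, as the trial's actual power. The documents do not support this. It converts skewed quartiles by a normal rule, keeps a correlation that the plan itself calls conservative, and lets an RA cohort stand for the trial. If RA wrists differ persistently between patients, the correlation could be well above 0.1; at ρ = 0.7 and SD 23.5 power is about 82%.
- **The trial's patients are selected.** Eligibility requires an exacerbation refractory to cDMARDs with wrist arthritis as the main symptom, and excludes severe osteoarthritis with malformations and previous surgery of that wrist. Patients at the low end of the cohort should largely be absent. This could narrow the spread and is why SD 20 is in the table, but nothing in the article supports going down to 15.
- **The gap is partly disclosed.** The article says that RA SDs are not known, and the simulation code is a supplement that is not shown. Whether the code varied the SD cannot be checked, so the observation about sensitivity covers only the article.
- **A null result would be misread as ruling out an 11-point benefit.** One might infer this, but the document states no such reading, and how to interpret a non-significant result belongs to the analysis plan.

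These points widen the range and lower the certainty about its size. They do not restore 90% unless the SD is close to 15 or the correlation is far above the plan's own value.

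**Conclusion.** The point holds as a matter of an unsupported input. The stated 90% power is correct for SD 15.0 and ρ = 0.1, but the only patient data in the paragraph point to a clearly larger SD. At ρ = 0.1, power at 38 per arm is about 39–63% over SD 28.5 to 21, and about 67% at SD 20. At ρ = 0.5 it is about 49–79% over SD 28.5 to 20. At ρ = 0.1 the difference detectable with 90% power is about 15 to 21 points over SD 20 to 28.5, against the target of 11.

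The direction is secure; the exact size is not. These figures assume a two-sided test, the same SD at baseline and at 3 months, an SD recoverable from published quartiles, and trial patients about as variable as the cited RA cohort (or somewhat less so, in the SD 20 case). No figure for PsA patients or for the post-treatment spread is given.

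**What to change.** 1. Rerun the existing simulation code with RA-based SDs.
2. In the abstract's Methods and in the Sample size section, restate power and the detectable difference as a range over SD 15 to 28.5 and ρ 0.1 to 0.5. Name the source and assumption behind each SD, and remove the statement that 80 patients are sufficient.
3. While recruitment is open, compute the PRWE SD and the baseline/3-month correlation on all patients together, without splitting by arm, and report the power they imply. The unsplit 3-month SD is only slightly inflated by a true treatment difference: 11 points adds 11²/4 = 30.25 to the variance, so an SD of 23.5 would appear as √(552.25 + 30.25) = 24.1. The baseline SD is unaffected.

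The cost is rewording, a rerun of existing code and one calculation that compares no arms. No added patients are required for this. The price is a less favourable stated power: the change makes the claim accurate and does not itself bring the trial to 90%.
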